### Study within a trial

A study within a trial will evaluate the impact of a pen and a brief PIS on levels of participant recruitment, using a factorial embedded RCT. Patients were randomised to: (1) A pen with the trial logo printed on, in addition to the standard invitation materials; (2) A pen with the trial logo printed on, in addition to a brief PIS, and the standard invitation materials; (3) A brief PIS and the standard invitation materials or (4) The standard invitation materials alone.

### Ethics and dissemination

#### Safety

Adverse events (AEs) may be identified during participant consultations or from self-report measures. We will only collect AEs defined as ‘expected’ for this trial which include (A) significant exacerbation of mental distress defined as a PHQ-9 score of 20 or more and/or a score of 2 or 3 on question 9 (suicidality item), representing at least a 1 point score change (ie, a change from 2 to 3 from their previous measure), (B) self-harm and (C) emerging serious mental illness or substance use disorder identified after randomisation. All AEs which meet the definition of serious AE (SAE) will be collected and assessed for relatedness to the intervention. Related SAEs will be reported to the Sponsor and the Research Ethics Committee.

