#### Randomisation and blinding

Following consent and baseline data collection, participants were individually randomised (1:1) to the symptoms clinic plus usual care or usual care alone, using a computer generated pseudorandom list, stratified by study centre with random permuted blocks of varying sizes. Allocation was concealed using a centralised web-based randomisation system.

The participant was then randomised and informed of their allocation. If assignment was to the intervention, the first symptoms clinic appointment was scheduled. If assignment was to usual care alone participants were reminded to use their usual healthcare services (eg, usual care GP) as required.

Due to the nature of the intervention, it is not possible to blind participants to their allocation. For practical reasons such as coordinating symptoms clinic appointments and ER-GP supervision some members of the research team are not blinded, including the trial manager and chief investigator (CI).

Members of the trial steering committee (TSC), study statisticians, health economists and those collecting outcome data are blinded to treatment allocation while the trial is ongoing.

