### The symptoms clinic

The symptoms clinic intervention is a sequence of medical consultations which aim to elicit a detailed clinical history, ensure that the patient’s experience is fully heard and validated, to offer rational explanations for symptoms and to assist the patient to develop ways of managing their symptoms. The treatment model can be summarised under four headings: Recognition, Explanation, Action and Learning (see online supplemental materials 3 for further details).

10.1136/bmjopen-2022-066511.supp3Supplementary data

Consultations before March 2020 were delivered face to face. Subsequently consultations took place via video consultation or telephone. The symptoms clinic consists of up to four consultations; an initial long consultation (approximately 50 min) followed by up to three medium length consultations (15–20 min) approximately every 2 weeks. Clinicians had flexibility to increase the gaps between sessions if required.

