### Outcomes

The primary outcome is the PHQ-15^26^ at 52 weeks postrandomisation. The PHQ-15 consists of 15 items for which patients are asked to report symptom severity over the past 4 weeks on a scale of 0 (not bothered at all), 1 (bothered a little) or 2 (bothered a lot). It has excellent internal reliability (α=0.80) and good convergent validity with other measures of functionality, symptom severity and disability days.^26^

The secondary outcomes are:

Quality of Life measured using the EuroQol 5 dimension 5 level version (EQ-5D-5L).^27^ In addition we will collect data for Short-Form Six Dimension (SF-6D)^28^ derived from the 12-Item Short Form Health Survery (SF-12) and ICECAP-A^29 30^ to compare their performance in this study population.Symptoms of depression and anxiety using the PHQ-9^31^ and Generalised Anxiety Disorder-7.^32 33^Healthcare resource (HCRU) use over the 52-week period using both self-report (a bespoke resource use questionnaire capturing healthcare use, in primary and secondary care as well as NHS and private services) and medical case note review of GP records.Patient-reported Global Indicator of Change.Ability to Participate in Social Roles and Activities - Patient Reported Outcome Measurement Information System (PROMIS)^34^

In addition, we will measure:

Somatic Symptoms Disorder-B criteria scale-12.^35^European Health Literacy Survey-6.^36^

We are also collecting data on whether the participants have experienced symptoms of COVID-19.

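### Self-harm, emerging serious mental illness or substance use disorder, and serious adverse events have no stated ascertainment route that is equal between arms

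*Protocol article*

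**What the plan says.** The Safety section of the protocol article gives two routes for finding adverse events: "Adverse events (AEs) may be identified during participant consultations or from self-report measures". It then limits collection to three expected categories. Category A is defined by score: "significant exacerbation of mental distress defined as a PHQ-9 score of 20 or more and/or a score of 2 or 3 on question 9", with at least a one-point change. The other two are defined by event: "B) self-harm and (C) emerging serious mental illness or substance use disorder identified after randomisation". For serious events it says "All AEs which meet the definition of serious AE (SAE) will be collected and assessed for relatedness to the intervention" and names no further source.

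On contact with participants, the section on the intervention says "The symptoms clinic consists of up to four consultations; an initial long consultation (approximately 50 min", followed by up to three shorter ones about two weeks apart. For the other arm, Randomisation and blinding says "If assignment was to usual care alone participants were reminded to use their usual healthcare services (eg, usual care GP) as required".

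Questionnaires go to everyone at enrolment and by post at 13, 26 and 52 weeks (Data collection and management). The Outcomes section also plans a "medical case note review of GP records". Its stated purposes there and under Health economics are healthcare resource use and cross-validation of self-report.

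**The concern.** A harms comparison is interpretable only if an event has a similar chance of being recorded in either arm. Clinic sessions are long, take a detailed history and invite disclosure, so they are a likely place for self-harm or substance use to come to light. Usual-care participants have no matching trial contact. Their GP is told of participation and allocation (Usual care section) but is given no adverse-event reporting role.

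With equal true risk, the arm that is observed more will show more events. The data monitoring and ethics committee reviews trial data and advises on patient safety and trial continuation (Governance section), and a final report would normally tabulate harms by arm. With small counts, unequal detection could suggest harm that is not there or hide a real reduction.

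**Working it through.** **Step 1: match each event type to its stated routes.**

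| Event type | Clinic consultations | Self-report measures | GP-record review |
|---|---|---|---|
| A (PHQ-9 score) | not needed | PHQ-9, same schedule in both arms | not needed |
| B (self-harm) | intervention arm only | no instrument described as measuring it; item 9 is labelled a suicidality item, and self-harm is a separate category | both arms, but not named as a source |
| C (serious mental illness, substance use disorder) | intervention arm only | no instrument described as measuring it; PHQ-9 and GAD-7 cover depression and anxiety | both arms, but not named as a source |
| Serious events | intervention arm only | none stated; resource-use form may give indirect signals | both arms, but not named as a source |

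Category A has a symmetric route. The other rows do not.

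**Step 2: direction.** Recorded risk = true risk × detection sensitivity. If true risks are equal, the recorded risk ratio equals the ratio of the sensitivities. An extra route in one arm pushes it above 1 for the intervention.

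**Step 3: size.** The document gives no event rate and no detection rate, so there is no plan figure to reproduce. The inputs are:

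- Participants per arm: 354 / 2 = 177 (Abstract, 1:1 allocation).
- Clinic window: four consultations about two weeks apart span 3 × 2 = 6 weeks. I take 6 to 12 weeks from randomisation to last consultation; the upper end is an assumption that allows for scheduling and longer gaps.
- True yearly risk of a category B or C event: 5% assumed, with 2% and 10% as the range.
- Detection in consultations, for events up to the last one: 60% assumed.
- Events spread evenly over 52 weeks: assumed.

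Expected true events per arm at 5%: 177 × 0.05 = 8.85.

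Events falling inside the window: 8.85 × 6/52 = 1.02 to 8.85 × 12/52 = 2.04.

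Detected in consultations: 1.02 × 0.6 = 0.61 to 2.04 × 0.6 = 1.23.

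At 2% risk (3.54 events) the same steps give 0.25 to 0.49. At 10% (17.7 events) they give 1.23 to 2.45.

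**Step 4: allow for some detection in both arms.** Suppose a common route, such as the resource-use questionnaire, finds 20% of events in either arm (assumed). Sensitivity in the intervention arm becomes 0.2 + 0.8 × 0.6 × w, where w is the share of the year inside the window.

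- w = 6/52: 0.2 + 0.055 = 0.255. Recorded events are 2.26 against 1.77, a ratio of 1.28.
- w = 12/52: 0.2 + 0.111 = 0.311. Recorded events are 2.75 against 1.77, a ratio of 1.55.

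The excess is then 0.5 to 1.0 event at 5% risk.

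**The case against.** Several points on the other side are sound.

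- The article states no between-arm analysis of adverse events. The uses it states are collection, assessment of serious events for relatedness, and reporting of related ones. Extra contact in one arm does not undermine those uses. This stands: the bias is a risk to a comparison that someone will probably make, not an error in a specified test.
- The source sentence is permissive and does not define participant consultations. Reading the term as clinic sessions is the natural inference, but it is an inference. If usual-care GP visits were meant, the article describes no route by which their content reaches the trial.
- The bespoke resource-use questionnaire is a self-report measure, is given at 26 and 52 weeks without restriction by arm, and may reveal some events indirectly. Its items are not shown. A reader might infer that usual-care events are almost undetectable; the document does not support that.
- A reader might also infer that all harms comparisons are biased, or that a several-fold excess is to be expected. Neither follows. Category A is collected alike in both arms. A large excess requires high consultation detection to apply to the whole year, whereas a consultation cannot find an event that happens after the last session.
- A condensed article may leave source recording to a fuller document. That answers a complaint about missing detail. It does not answer the point that the two sources the article does name are unequal between arms for these events.

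**Conclusion.** The point holds for categories B and C and for serious events: following the Safety section as written gives the intervention arm a detection route that usual care lacks. It does not hold for PHQ-9-defined events, given similar questionnaire return in the two arms.

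The expected direction is more recorded events in the intervention arm, concentrated in the clinic period. The size cannot be derived from the document. Under the stated assumptions it is about one event (0.6 to 1.2 at 5% yearly risk; 0.2 to 2.5 across risks of 2% to 10%). The window would be longer where gaps were extended or where the pandemic pause delayed the clinic. An excess of one event is small in absolute terms, but it can change the reading of a table whose cells hold only a few events. The conclusion rests on reading participant consultations as clinic sessions and on no unlisted usual-care route existing.

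**What to change.** 1. Record the source of every adverse event: clinic consultation, questionnaire, GP record or other.
2. Add category B and C events and hospital admissions to the standardised GP-record extraction form, for both arms.
3. Base any between-arm comparison on sources common to both arms: PHQ-9 at 13, 26 and 52 weeks, and the record review.
4. List consultation-detected events separately and descriptively. Keep all existing safety reporting unchanged.

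The clinic doctor writes to the participant's GP after the first and last appointments, so an event disclosed in clinic can enter the GP record by that letter. Flag record entries whose only origin is such a letter and leave them out of the common-source comparison.

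The cost is a few fields on a form that is already planned and a footnote to the harms table. Extraction is scheduled after all other participant measures, so the change does not threaten the blinding of those measures. The downside is that record-based events are found late, only where records are available, and only if the GP knew of them. These limits apply to both arms.

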#### Inclusion and exclusion criteria

Inclusion criteria:

Aged between 18 and 69 years (inclusive) at the time of the computer search.Current physical symptoms which meet the below criteria.Clinical records suggest PPS.Records show at least two referrals for specialist opinion in the last 36 months (extended to 42 months when restarting after the first pandemic wave).Records show no evidence of any previous or current major illnesses likely to cause multiple symptoms.Doctors in the GP practice do not believe that the majority of the patient’s symptoms can be currently explained by other pathology.The score on the Physical Health Questionnaire-15 (PHQ-15) is between 10 and 20 (inclusive).Access to a mobile phone with video calling capability or an email address and computer with video conferencing capability.

Exclusion criteria:

A score of 3 on question 9 on the PHQ-9 completed at the enrolment appointment.Difficulty conducting a healthcare consultation in English without either a professional or family interpreter or other assistance.The GP regards inviting them to participate as inappropriate (eg, recent bereavement).Severe symptom-related disability (eg, requiring help with daily personal care or severely impaired mobility).Undergoing active multidisciplinary rehabilitation, Improving Access to Psychological Therapies (IAPT) programme or specialist psychological treatment including specialist pain, fatigue or other symptom clinic at the time of screening.Currently pregnant or less than 6 months postnatal at the time of the screening telephone call.

A three-stage identification process was adopted: computer searching, GP record screening and postal invitation.

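### The suicidality part of expected adverse event (A) is internally inconsistent: the general wording admits five upward changes on question 9, while the bracket that restates it admits only 2 to 3

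*Protocol article*

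**What the plan says.** The Safety section of the protocol article limits adverse event collection to events defined as expected for the trial and lists three categories, (A) to (C). Events that meet the serious definition are all collected as well.

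Category (A) opens with "significant exacerbation of mental distress defined as a PHQ-9 score of 20 or more". Joined to this by and/or is a second criterion: "a score of 2 or 3 on question 9 (suicidality item"). Then comes a qualifier, followed at once by a bracket that restates it: "representing at least a 1 point score change (ie, a change from 2 to 3 from their previous measure").

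The only other rule on this item is an exclusion under Inclusion and exclusion criteria: "A score of 3 on question 9 on the PHQ-9 completed at the enrolment appointment". No other section restates or clarifies the adverse event definition.

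**The concern.** *Ie* means *that is*. What follows it should say the same thing as what came before, and here it does not. The general words describe a set of changes that end at 2 or 3. The bracket describes a single change that ends at 3.

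This is an operative definition and not background text, because the trial collects only the listed expected events. If the bracket is applied as printed, a participant who rises from 0 or 1 to 2 or 3 on the suicidality item is not collected under this part of category (A). If the general words are applied, the same participant is. According to the Governance section, the data monitoring and ethics committee reviews the trial data and advises on patient safety, so the content of that category matters.

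A smaller uncertainty sits in the same sentence. It is not clear whether the change condition qualifies question 9 alone or also the PHQ-9 total of 20 or more. If it does not reach the total, a participant whose total stays at or above 20 would meet a definition headed as an exacerbation without having worsened.

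**Working it through.** There is no stated figure to reproduce. The check lists the changes that each half of the sentence admits.

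**Inputs**
- Qualifying current scores, general wording: 2 or 3 (Safety).
- Size of change, general wording: at least 1 point, with no direction written (Safety).
- Direction: a rise, inferred from the word exacerbation at the head of category (A).
- Bracket: previous score 2, current score 3 (Safety).
- Item range: 0 to 3. This is an assumption, because the article does not print the range.

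**Enumeration**

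With four possible scores there are 4 × 4 = 16 pairs of previous and current score. The general rule is: current score in {2, 3} and current − previous ≥ 1. The bracket rule is: previous = 2 and current = 3.

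| Previous to current | Rise | General wording | Bracket |
|---|---|---|---|
| 0 to 2 | 2 | in | out |
| 1 to 2 | 1 | in | out |
| 0 to 3 | 3 | in | out |
| 1 to 3 | 2 | in | out |
| 2 to 3 | 1 | in | in |

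The general wording admits 5 changes and the bracket admits 1, so 5 − 1 = 4 are in dispute. They include 0 to 3, the largest rise the item allows.

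**Whether the bracket can be squared with the words before it**
1. The only change it admits ends at 3. No admitted change ends at 2, so naming a score of 2 as a trigger would have no effect.
2. The rise is 3 − 2 = 1 point exactly, so *at least* would have no effect either.

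The two halves therefore cannot both be the rule.

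**The case against.** The strongest reply is that only one reading gives effect to every word. A bracket that empties both *a score of 2* and *at least* is most naturally a slip of *ie* for *eg*, with 2 to 3 meant as an illustration. That is the probable explanation. It explains how the sentence came about, but the text as printed still defines two different sets of events, and the authors have to confirm which one they meant.

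A second reply is that this is a condensed article, and the full protocol, procedures and case report forms may be clear. That may be so. However, the article does not omit the rule; it states one that conflicts with itself, and a clear rule elsewhere would only make the correction easier.

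Third, the consequences are partly contained. Self-harm and new serious mental illness are separate categories, all serious events are collected, and the PHQ-9 is itself an outcome, so the scores exist whatever label is given. This stands, and it limits the harm.

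Some stronger readings are tempting but not supported:
- *A fall from 3 to 2 would count.* The word *change* taken alone allows it, but the event is an exacerbation, which settles the direction.
- *Most new suicidality would be missed.* Four of five is a count of types of change, not of participants, and the article gives no frequencies.
- *Staff apply the rule differently over time or between arms.* The article does not describe how assessors use the sentence and reports no inconsistency.
- *The enrolment exclusion of a score of 3 narrows the bracket at first follow-up.* The bracket needs a previous score of 2 at any visit, whatever the enrolment rule says.

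**Conclusion.** The question 9 part of expected adverse event (A) is wrong as written. Its general wording and its bracket give two different sets of collected events, five types of upward change against one, and under the bracket a score of 2 could never trigger the event.

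The count rests on two assumptions: that the item is scored 0 to 3, and that *change* means a rise. The two internal conflicts, over the score of 2 and over *at least*, follow from the printed words without needing the lower end of the range.

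The defect is one of wording in a safety definition. It touches no efficacy, sample size or economic result, and the documents do not show that any event has been misclassified. It is still worth correcting, because the trial collects only the listed expected events. Whether the change condition reaches the PHQ-9 total is a point to clarify and not a contradiction.

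**What to change.** Reconcile the general wording and the bracket into one rule that:
- marks each of the five upward changes as counted or not counted;
- says whether the change condition applies to question 9 alone or also to the PHQ-9 total of 20 or more.

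Which changes should count is a clinical decision for the trial team, and none is proposed here.

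Once the rule is settled, check questionnaire-based events against the PHQ-9 item scores collected in both arms at baseline, 13, 26 and 52 weeks. Restate reported counts only if that check shows a discrepancy. The check cannot cover events picked up in consultations, which the Safety section also allows as a source.

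The cost is a one-sentence wording change and a short tabulation of data already collected. The possible downside is that some adverse event counts may have to be restated.

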#### Governance

Sheffield Clinical Trials Research Unit on behalf of the Sponsor (NHS Sheffield Clinical Commissioning Group, [name]) coordinates the trial. The CI, project coapplicants, members of the data management team, sponsor, trial manager and other representatives form the TMG, who oversee the operation of the trial and through which amendments will be communicated. The TSC, comprised two clinicians, a statistician, Health Economist and PPI representative, provides independent oversight. The independent DMEC comprised two clinicians and a statistician reviews the trial data and advises the TSC on issues of patient safety and trial continuation.

#### Ethics approval

This trial was approved by Greater Manchester Central Research Ethics Committee, reference 18/NW/0422), on 25 June 2018. The committee will be notified of any amendments to the trial protocol as appropriate.

#### Dissemination

We will publish the study’s findings in peer-reviewed academic journals and present at local, national and international conferences where possible. We will publish a short summary of the results on the MSS3 website that can be accessed by all trial participants as well as relevant interest groups.
